#### Depression and Anxiety in Stroke Survivors

Psychological and affective disorders often occur after a stroke. The most common are depressive and anxious symptoms. Prevalence of depression ranges from approximately 20 to 40% (Barkercollo, 2007; De Wit et al., 2008; Ayerbe et al., 2011, 2013) and prevalence of anxiety is estimated between 18 and 32% in general stroke survivors’ population (Barkercollo, 2007; Ayerbe et al., 2014; Schöttke and Giabbiconi, 2015).

Several studies focused on depression after a stroke. In comparison, very few studies have been published considering specifically minor stroke patients while the prevalence of depression has been estimated at the same rates than in general stroke survivors populations (Altieri et al., 2012; Shi et al., 2015).

Not only it appears essential to identify and to treat post-stroke depression (PSD) and post-stroke-anxiety (PSA) because of their symptoms burden but also because of their negative impact on functional outcomes and mortality after stroke (Chemerinski et al., 2001; Naess et al., 2010; Bartoli et al., 2013).

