### Objectives

This article aims to describe an innovative study design for the assessment and investigation during 4 months (following stroke), of minor stroke patients’ psychological health (depression, anxiety), coping strategies and quality of life combining classical standard scales and questionnaires with EMA using a smartphone application.

Primary objective is a methodological one. We aim to evaluate feasibility, acceptability, quality and reliability of data collected by EMA in minor stroke patients at different times and in different contexts during the first 4 months following a stroke.

Secondary objectives focus on studying psychopathological manifestations after stroke and the processes involved in their onset and evolution. Thus, we have several objectives considering these points: (1) to estimate the frequency and assess the evolution of anxiety and depression in minor stroke population, (2) to determine the risk factors and determinants of PSA and PSD in minor stroke patients and to study if coping is a reliable predictor, (3) to describe the clinical and psychosocial characteristics of depressed and anxious individuals after a minor stroke, (4) to describe symptomatic characteristics of PSD and PSA, (5) to study the sequences and dynamic processes between anxiety and depression symptoms, coping strategies and contextual and ecological factors at different times (during the first days, at 2 months and at 4 months) and contexts (hospitalization, discharge, return to work) after stroke.

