#### EMA and Ad Scientiam Tool

In this study, the EMA is designed as a smartphone application: Ad Scientiam Research^®^. The app is programmed on participants’ personal (or lent) smartphones.

Each EMA phase (phase 1b = hospital discharge, phase 2 = 2 months post stroke and phase 3 = 4 months post stroke) lasts 1 week. The participants answer four brief electronic interviews (<3 min) per day during 7 days. The app sends prompts to inform the participants that they can answer the interview.

Time of prompts are fixed for each patient and randomized across patients. They occur within each of the following time periods: 7–10 am, 11 am to 2 pm, 3–6 pm and 7–10 pm. Each prompt is spaced out of at least 2 h from the prior and next prompts. A randomly generated daily schedule is submitted to participants. The time of prompts can be adjusted at each phase in order to suit participants’ typical daily schedules (wake, work, and sleep). The application permits responses to be provided within 30 min after each prompt.

The EMA consists in 32 screens related to seventeen questions split into three questionnaires (the exact wording is available in Supplementary File 1): (1) present situation and context; (2) anxiety and depression symptoms; (3) positive and negative events.

The selected items are based on previous EMA studies (Jean et al., 2013) or built specifically for the study on the basis of validated questionnaires. Questions composing questionnaire 2 have been adapted from the MINI (Major Depressive Episode and General Anxiety Disorder modules; Lecrubier et al., 1997; Sheehan et al., 1998). The anxiety and depression symptoms that can possibly variate within a day as it was previously done for an EMA study of depression in stroke population (Sibon et al., 2012) have been selected. For the questionnaire 3, questions about positive and negative events have been adapted from the Inventory of Small Life Events (Zautra et al., 1986) previously used and adapted for EMA (Petit, 2009; Mazure et al., 2014). Questions about the coping strategies for facing the negative event have been adapted from the Brief-COPE (Carver, 1997) and is an original EMA measure of coping created for the present study.

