###### Medical condition and treatment

Data about the medical condition of the participants including previous and present affections (somatic, neurologic, psychiatric), family history neurological affections, medical treatment at hospital entrance, vascular risk factors (BMI, diabetes, cholesterol, high blood pressure, alcohol and other substance use).

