##### Outcomes and statistical methods for secondary objectives

(1) Frequency will be estimated as the ratio of depressed and anxious participants to the total number of participants. Presence of depression and anxiety will be determined in two different ways: according to the examination of psychiatric disorders during the semi-structured interview; and as a function of the cut-off scores of self-reported questionnaires and clinicians’ ratings scale previously reported in the instruments section.

(2) Univariate logistic regression analysis will be performed to study if the clinical variables (subtypes of anxiety and depression symptoms, coping strategies) predict depression and anxiety within each time and between times of the study.

(3) Descriptive analysis will be performed on clinical, sociodemographic and medical measures to describe depressed and anxious participants. Their results will be compared to healthy participants (presenting no significant depression and anxiety) with Chi-square and Student’s *t*-test.

(4) We will examine whether EMA of the different symptoms of depression and anxiety are associated with self-report and clinician-rated depression and anxiety to describe characteristics of PSD and PSA. Means-as-outcomes modeling will be used to describe those associations.

(5) In order to describe the time dynamics between anxiety and depression symptoms, coping strategies and contextual settings assessed with EMA, we will use a Multilevel Vector Autoregressive method (Bringmann et al., 2013). With the Vector Autoregressive (VAR) model, each variable at time point *t* is regressed to the time point *t* – 1 of every other variable. For example, sadness at 1 pm is regressed with all other depression and anxiety symptoms (including sadness) at 10 am. The multilevel-VAR model is suited to the hierarchical structure of EMA data and it enables to describe population dynamics as a function of within-person variability.

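### Between-times prediction of depression and anxiety is fixed as univariate logistic regression on caseness, without the earlier symptom score the study already collects, so a coping result can reflect persisting distress

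*Protocol article*

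**What the plan says.** The second secondary objective (Objectives) is "to determine the risk factors and determinants of PSA and PSD in minor stroke patients and to study if coping is a reliable predictor". The method assigned to it, in item (2) of Outcomes and statistical methods for secondary objectives, is: "Univariate logistic regression analysis will be performed to study if the clinical variables" (symptom subtypes and coping strategies) "predict depression and anxiety within each time and between times of the study".

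Item (1) of that section makes the outcome binary. Presence of depression or anxiety is set either by the diagnostic interview or "as a function of the cut-off scores of self-reported questionnaires and clinicians’ ratings scale previously reported in the instruments section".

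Three other places bear on the choice:

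- Table 1 shows that earlier scores exist: MADRS and HAM-A in hospital (phase 1a) and at 4 months (phase 3); BDI-II and HADS at discharge (1b), 2 months (2) and 4 months (3). Brief-COPE is taken at 1b, 2 and 3.
- The background section on symptomatic components says that emotional symptoms in the acute phase forecast later levels of depression.
- The anticipated results for the secondary objectives read coping directionally, with active coping expected to bring about less anxiety and depression.

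**The concern.** A univariate between-times model compares later cases and non-cases on one earlier variable. Patients who are already distressed at discharge may cope differently, and by the article's own background they are more likely to be depressed later. Without the earlier score, the model cannot tell coping that adds information about later mood from coping that only marks mood already present. Objective 2 asks about determinants and about coping as a reliable predictor, so this distinction is the question being asked.

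There is a second cost. BDI-II, HADS, MADRS and HAM-A are graded scores. Cutting them into yes/no in a sample of 30 to 36 discards information, and leaving out a strong prognostic variable leaves its variation in the error.

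The within-time models are cross-sectional. They cannot show direction with or without adjustment.

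**Working it through.** **1. Sample size, reproduced.** The Sample Size section includes 40 participants and expects 75 to 90% acceptance: 40 x 0.75 = 30 and 40 x 0.90 = 36. This matches the stated 30 to 36. The article gives no alpha, power or effect size for this analysis, so there is no power figure to reproduce.

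**2. Expected cases.** The background says: "Prevalence of depression ranges from approximately 20 to 40" per cent; for anxiety it gives 18 to 32%. The Discussion expects minor stroke to be similar.

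- Depression: 30 x 0.20 = 6 to 36 x 0.40 = 14.4.
- Anxiety: 30 x 0.18 = 5.4 to 36 x 0.32 = 11.5.
- If all 40 supply questionnaires: 8 to 16 depressed and 7.2 to 12.8 anxious.

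**3. Simulation model.** B is baseline distress, C the earlier coping score and Y the later symptom score, all standardised. Y is cut at the article's depression prevalences (20 to 40%) to give caseness. Tests are two-sided at 5%: likelihood ratio for univariate logistic regression of caseness on C, and t-test for C in linear regression of Y on C and B. Assumed, because the article gives none of them: the 5% level, corr(C,B) of 0.2 to 0.5, corr(B,Y) of 0.5 to 0.6, and a true effect of 0.4 SD.

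**4. Coping has no effect of its own.** C and Y are then correlated only through B, with correlation corr(C,B) x corr(B,Y).

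| corr(C,B) | corr(B,Y) | Induced corr(C,Y) | Univariate logistic significant | Adjusted linear significant |
|---|---|---|---|---|
| 0.2 | 0.5 | 0.10 | about 8-9% | about 4-6% |
| 0.3 | 0.5 | 0.15 | about 10-13% | about 4-6% |
| 0.5 | 0.6 | 0.30 | about 22-31% | about 4-6% |

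Ranges cover n = 30 and 36 and prevalence 20 to 40%. Repeat runs move the ends by up to about three points.

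**5. True effect of 0.4 SD, C unrelated to B, corr(B,Y) 0.6.** Univariate logistic power is about 34 to 51%; adjusted linear power is about 81 to 89%. Hand check of the second figure: residual SD = sqrt(1 - 0.36 - 0.16) = 0.693. The expected t is 0.4/0.693 x sqrt(27) = 3.00 at n = 30 and 0.577 x sqrt(33) = 3.32 at n = 36, which by a normal approximation gives roughly 83% and 90%. Dichotomising alone (unadjusted linear against unadjusted logistic) costs about 16 to 29 points.

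**6. True effect of 0.4 SD, C correlated with B, prevalence 30%, total corr(B,Y) held at the stated value.**

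| corr(C,B), corr(B,Y) | Univariate logistic, n = 30 / 36 | Adjusted linear, n = 30 / 36 |
|---|---|---|
| 0.3, 0.5 | 65% / 70% | 70% / 77% |
| 0.5, 0.6 | 80% / 85% | 67% / 75% |

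In the second row the univariate test rejects more often, but part of that rejection is the confounding shown in step 4. The power gain from adjustment is small or absent here; what adjustment buys is a test that addresses coping rather than baseline mood.

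**The case against.** **The size depends on assumptions.** This stands. At weak correlations the false-positive rate is 8 to 9%, not far above nominal. A reader might infer that early distress will certainly pass as a coping effect, but the article gives no correlation between coping and mood, so only the conditional statement is supported. The bias and power figures also need different assumptions and must not be quoted as one scenario.

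**Adjustment has its own interpretation.** This also stands. Coping and mood at phase 1b are measured together, and mood may partly result from coping. The adjusted estimate then asks whether coping predicts later symptoms beyond current mood, which is narrower than total association. The MADRS and HAM-A route is less exposed, since those baselines are taken in hospital, before the first Brief-COPE.

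**One predictor per model is a usual response to few events.** True of logistic regression. With about 5 to 14 cases, adding a covariate to the logistic model is fragile: separation occurred in some simulated runs, and the test was mildly anti-conservative. That argues for the continuous score, not for leaving baseline out.

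**The detail may sit in an unseen analysis plan.** The article does not leave the method open; it names a univariate model.

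**Stronger readings that are not supported.**

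- Multiplying predictors, outcomes and phases into a count of expected false positives. The article speaks of symptom subtypes without numbering them, gives no alpha, and such a count needs every null to be true.
- Calling the within-time models circular in general. It is true that "Questions composing questionnaire 2 have been adapted from the MINI", but the MINI is given only at phases 1a and 3 and EMA starts at 1b, so the overlap with a MINI outcome in the same phase can arise only at phase 3. It does not touch coping.
- Adding later care to the models because only "medical treatment at hospital entrance" is recorded. Care begun after discharge follows from distress and comes after the exposure; adjusting for it can introduce bias.

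**Conclusion.** The point holds for the between-times models. A univariate logistic model on caseness cannot separate coping as a predictor from persistence of existing distress, and the variables needed to do so are already in Table 1. With coping given no effect of its own, the planned test is significant in about 8 to 31% of runs, against about 5% for the baseline-adjusted linear model. This assumes predictor-baseline correlations of 0.2 to 0.5, baseline-outcome correlations of 0.5 to 0.6, and n of 30 to 36. The loss of power (34 to 51% against 81 to 89%) applies to a 0.4 SD effect unrelated to baseline. A reader might take it as a general halving of power; step 6 shows that it is not.

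The multilevel VAR model planned for objective 5 uses lagged symptoms within the EMA data. It does not adjust later depression for baseline, so it does not fill this gap.

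This is one secondary objective of a study whose primary aim is methodological. The change should be made, but the feasibility and validity analyses do not depend on it.

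**What to change.** Reword item (2) for the secondary objectives as follows.

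- **Between times:** linear regression of the later continuous score on the earlier predictor plus the earlier score of the same scale. Use BDI-II or the relevant HADS subscale from 1b to 2, 1b to 3 and 2 to 3, and MADRS or HAM-A with the phase 1a score as baseline and phase 3 as outcome. Report estimates with confidence intervals.
- **Caseness:** keep the univariate logistic results as descriptive support.
- **Within time:** report as associations, not prediction.
- **Status:** label the whole set exploratory.

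The cost is analysis wording and one extra model term; no visit, instrument or participant is added. Coefficients will be in scale points instead of odds ratios. The write-up must say that the adjusted estimate concerns prediction beyond current mood.

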#### Sample Size

Forty participants will be included in the study. According to previous research using EMA for psychological assessment, an acceptance rate between 75 and 90% is expected (Johnson et al., 2009a,b). Thus, we expect data from 30 to 36 participants to perform analysis.

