#### Secondary Objectives

We expect frequency of depression and anxiety in minor stroke population to be as high as frequency in general stroke. Indeed, even if the motor and cognitive impairments after a more severe stroke could lead to more severe anxiety and depression, previous study about prevalence of depression after minor stroke is in the range of prevalence found in general stroke population (Shi et al., 2015).

In line with previous results about PSD (Carota et al., 2005; Sibon et al., 2012; Lerdal and Gay, 2013), the results about the ecological characteristics of depression and anxiety after minor stroke could reveal different symptoms’ profiles as a function of time. Depression and anxiety at phase 1 would be characterized more by physical and non-specific symptoms such as fatigue, physical tension, attention difficulty whereas phase 2 and 3 profiles would have different profiles characterized by more specific symptoms.

Even if the investigation of time dynamics between depression and anxiety symptoms is greatly exploratory, we have similar expectations regarding the evolution of the importance and centrality of physical symptoms as function of time. Indeed, physical and non-specific would lead to more specific symptoms at phase 1 than at phase 2 and 3.

Results about coping strategies could follow the same pattern, with different adaptive and maladaptive coping at phase 1, 2, and 3. In regard of previous research (Darlington et al., 2007; Rochette et al., 2007), active coping would lead to less anxiety and depression at phase 1 than later.

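### The univariate logistic regressions rest on about 5 to 14 expected cases. If fitted by standard maximum likelihood, the odds ratios will be very imprecise and, where an effect exists, biased away from 1.

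*Protocol article*

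**What the plan says.** All sections below are in the Protocol article.

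- **Method.** Outcomes and statistical methods for secondary objectives, item (2): "Univariate logistic regression analysis will be performed to study if the clinical variables", meaning symptom subtypes and coping strategies, "predict depression and anxiety within each time and between times of the study". The estimator, the type of interval and the handling of a model that does not converge are not described.
- **Sample.** Sample Size: "Forty participants will be included in the study", "an acceptance rate between 75 and 90% is expected", and so "we expect data from 30 to 36 participants to perform analysis".
- **Frequency of the outcomes.** Depression and Anxiety in Stroke Survivors: "Prevalence of depression ranges from approximately 20 to 40" percent; for anxiety, "prevalence of anxiety is estimated between 18 and 32" percent. The Discussion, under Secondary Objectives, carries these rates over to the study population: "We expect frequency of depression and anxiety in minor stroke population to be as high as frequency in general stroke".
- **Predictors.** EMA symptoms are on 7-point scales. The Brief-COPE gives 14 subscales of two four-level items each. EMA coping is 14 yes/no items per prompt. The article does not say how any of these is coded in the regressions.
- **Who is analysed.** Under Limitations, patients who decline the smartphone part still complete the questionnaires and interviews.

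**The concern.** What a logistic model can support depends on the number of cases more than on the number of patients, and the article never works out the case count. With cases in single figures or the low teens, maximum-likelihood odds ratios have wide sampling distributions and Wald intervals behave erratically. When a real association exists, the estimates are also pushed away from 1 on average. With a sparse binary predictor, one cell of the two-by-two table can be empty, and then the odds ratio is zero or infinite.

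The second secondary objective asks what determines post-stroke depression and anxiety and whether coping predicts them reliably. The Clinical Implications section hopes to direct clinicians towards particular symptoms. Ranking symptoms and coping strategies by unstable, exaggerated odds ratios would be a weak basis for either use. This small-sample estimation problem is separate from confounding, multiplicity, or overlap between predictor and outcome.

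**Working it through.** **1. The plan's own figure.** 40 × 0.75 = 30 and 40 × 0.90 = 36. The stated 30 to 36 is reproduced.

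**2. Expected cases = N × prevalence.**

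| N | 18% | 20% | 32% | 40% |
|---|---|---|---|---|
| 30 | 5.4 | 6.0 | 9.6 | 12.0 |
| 36 | 6.5 | 7.2 | 11.5 | 14.4 |
| 40 (questionnaire models, if decliners are within the 40) | 7.2 | 8.0 | 12.8 | 16.0 |

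For models using EMA data this is 5.4 to 11.5 cases of anxiety and 6.0 to 14.4 of depression. At N = 30 and 18% the binomial 95% range is 2 to 10 cases, with a 35% chance of fewer than 5. At N = 36 and 40% the range is 9 to 20. Dropout by phase is not given, so the later-phase reduction cannot be quantified.

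**3. Bias with a continuous predictor.** Datasets were simulated with one standard normal predictor and fitted by maximum likelihood (ML) and by Firth's penalised likelihood. The true odds ratios per standard deviation are assumptions; the article gives none. Geometric-mean odds ratios:

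| True odds ratio | ML, N = 30, 18% | Firth | ML, N = 36, 40% | Firth |
|---|---|---|---|---|
| 2 | 2.3 to 2.4 | 2.0 | 2.2 | 2.0 |
| 4 | 5.7 | 4.1 | 5.0 | 4.1 |

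Where a range is shown, separate simulation runs differed slightly. On the log scale the inflation at a true 2 runs from ln 2.2 / ln 2 = 1.14 to ln 2.4 / ln 2 = 1.26. At a true 4 it runs from ln 5.0 / ln 4 = 1.16 to ln 5.7 / ln 4 = 1.26. At a true odds ratio of 1 there is no bias. The median ML estimate at a true 2 is only about 2.06 to 2.18, so the excess in the mean comes largely from a tail of extreme samples.

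**4. Imprecision.** At a true odds ratio of 2, 95% of ML estimates lie between 0.7 and 16 at the low end (N = 30, 18%) and between 1.0 and 6.7 at the high end (N = 36, 40%). This spread is larger than the bias.

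**5. Separation.** For a continuous predictor with a true odds ratio of 1 to 3, fewer than 1% of samples give no finite estimate.

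For a yes/no predictor endorsed with probability q and unrelated to outcome, with c cases among N, the chance that nobody among the cases or nobody among the non-cases endorses it is

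(1 − q)^c + (1 − q)^(N − c) − (1 − q)^N.

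Taking 20% prevalence gives 6 cases in 30 (30 × 0.20) and 7 in 36 (36 × 0.20 = 7.2):

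- N = 30, c = 6, q = 0.10: 0.531 + 0.080 − 0.042 = 0.57
- N = 36, c = 7, q = 0.10: 0.478 + 0.047 − 0.023 = 0.50
- N = 30, c = 6, q = 0.20: 0.262 + 0.005 − 0.001 = 0.27
- N = 36, c = 7, q = 0.20: 0.2097 + 0.0015 − 0.0003 = 0.21

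The range is 21 to 57%. The endorsement rates and the person-level yes/no coding are assumptions.

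**The case against.** **The estimator is not named.** A journal article may leave estimation details to a fuller plan, and Firth regression is still logistic regression. This is fair, and it is why the point is conditional on standard maximum likelihood. But unqualified logistic regression conventionally means maximum likelihood, the case counts follow from the article's own figures, and one line would settle the matter.

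**The effects are moderate and the bias small.** With one predictor per model there are already 5 to 14 events per variable. At a true odds ratio of 2 the median estimate is close to the truth. This stands: bias matters mainly for strong effects or at the low end of cases. Strong effects are not far-fetched for symptoms, since the Anticipated Results hope for correlations above 0.70 between EMA indexes and conventional scales. That expectation, however, concerns indexes and not single symptoms or coping.

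**Separation depends on coding.** Symptom and Brief-COPE scores are scaled. The yes/no EMA coping items recur at up to 4 × 7 = 28 prompts a week, so a person-level predictor could be a proportion. This stands.

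**Stronger readings to avoid.** A reader might infer that every odds ratio will be inflated, or that some models certainly cannot be fitted. The documents support neither. There is no inflation under a null effect, and with binary predictors the ML estimates from estimable samples sometimes fell below the true value. Non-estimability needs a sparse coding that the article does not state. Nor is 5 to 14 a fixed count: decliners may raise it to about 7 to 16 for questionnaire models, and cut-off definitions of a case may give other numbers.

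**Conclusion.** The concern holds in conditional form. The case counts follow directly from the article. Given maximum likelihood, poor precision is the main consequence. Average bias away from 1 comes second: in the settings simulated it is about 14 to 26% on the log scale for true odds ratios of 2 to 4, and nil at 1. An appreciable risk of empty cells, 21 to 57%, applies only if coping enters as a seldom-endorsed yes/no variable with 6 or 7 cases.

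These sizes rest on the quoted prevalences applying to minor stroke, as the article expects, and on assumed effect sizes, predictor distributions and endorsement rates. The matter concerns a secondary objective and leaves the primary feasibility aims untouched. It is still worth correcting, because the article intends to draw conclusions about determinants from these models.

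**What to change.** In item (2) of the statistical methods for secondary objectives:

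- specify Firth penalised logistic regression, with profile penalised-likelihood confidence intervals and tests;
- report the number of cases and of patients behind each model;
- describe these results as exploratory.

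The cost is about one line of text and slightly more analysis work with standard software; no new data are needed. Reported odds ratios will be smaller than under maximum likelihood. In the simulations penalisation removed nearly all the mean bias, and it gives finite estimates in separated samples. It cannot make 5 to 14 cases informative, so intervals will remain wide.

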##### During hospitalization (phase 1a)

Each patient admitted to the Neurovascular Intensive Care Unit of the Paris Saint-Joseph Hospital Group for a stroke is screened by a physician for inclusion and non-inclusion criteria. The investigator, a psychologist, then meets eligible patients in order to explain the study and to give them an information letter containing the objectives and procedure. Patients who agree to participate sign the consent and then are assessed for depression and anxiety during a semi-structured interview.

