##### At hospital discharge (phase 1b)

The psychologist investigator calls the patients to have an appointment in the first days following hospital discharge. Patients are met at home in order to start the EMA procedure. During this appointment, patients fill self-report questionnaires assessing depression, anxiety, quality of life and coping strategies with stroke related stress. After that, the investigator either installs the study application on patients’ personal devices or lent a device during the EMA procedure for patients who do not possess a smartphone. The content of the application is displayed and patients are trained to use it in order to resolve technical concerns and questions. After 2 days, patients are called by the investigator in order to check any problem and to reinforce the motivation to keep answering the prompts. At the end of the week, patients are informed by a phone call that they can disconnect from the app.

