#### Phase 3: at 4-Months after Stroke

The psychologist investigator phones the patients 4 months after stroke in order to set an appointment at patients’ home for an interview during which depression and anxiety symptoms for the last 2 weeks are assessed. They fill the same self-report questionnaires. After the interview, the participants answer EMA on the smartphone during 1 week.

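### Within-phase logistic models are said to show whether coping predicts depression and anxiety, but none has coping measured before the outcome, so they cannot tell which way an association runs

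*Protocol article*

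**What the plan says.** The Objectives section of the Protocol article frames secondary objective 2 in terms of determinants of post-stroke depression and anxiety, and asks whether coping is a dependable predictor of them. The matching analysis, item (2) under Outcomes and statistical methods for secondary objectives, reads "Univariate logistic regression analysis will be performed to study if the clinical variables", with coping strategies listed among those variables, "predict depression and anxiety within each time and between times of the study".

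Item (1) of the same section defines a case in two ways. One is by diagnosis, "according to the examination of psychiatric disorders during the semi-structured interview". The other is by thresholds on the rating instruments, "as a function of the cut-off scores of self-reported questionnaires and clinicians’ ratings scale".

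The schedule is as follows.
- **Phase 1a (hospital):** patients consent and "then are assessed for depression and anxiety during a semi-structured interview".
- **Phase 1b (home, after discharge):** "patients fill self-report questionnaires assessing depression, anxiety, quality of life and coping strategies with stroke related stress". The app is installed after that, and the EMA week follows.
- **Phase 2:** the same questionnaires come by post around the EMA week. There is no interview.
- **Phase 3:** a home interview covers the last 2 weeks, and the questionnaires are filled in as well. "After the interview, the participants answer EMA on the smartphone during 1 week".

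In the Discussion (Anticipated Results, Secondary Objectives) the article expects that "active coping would lead to less anxiety and depression at phase 1 than later".

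**The concern.** A predictor or determinant should be observed before the thing it is said to predict. If patients who are already depressed or anxious cope differently as a result, a model with coping measured at the same time or afterwards will show an association even when coping has no effect. A univariate model contains nothing that could separate the two explanations.

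At stake is what objective 2 can conclude. A significant within-phase odds ratio for a coping strategy could be read as support for coping as a determinant when the data are equally compatible with the opposite direction. The Limitations section discusses burden, reactivity to assessment, compliance and generalisability, but not this.

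**Working it through.** **Step 1: the plan's own figure.** Forty participants with 75% to 90% acceptance (Sample Size): 40 × 0.75 = 30 and 40 × 0.90 = 36. The stated 30 to 36 reproduces. With the depression prevalence of 20% to 40% quoted in the Introduction, the expected number of cases is 30 × 0.20 = 6 to 36 × 0.40 = 14.4, so about 6 to 14.

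**Step 2: order of measurement within each phase** (phase descriptions and Table 1).

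| Phase | Outcome | Brief-COPE | EMA coping |
|---|---|---|---|
| 1, interview | MINI, MADRS, HAM-A in hospital (1a) | later, at home (1b) | later still |
| 1, questionnaires | BDI-II, HADS at 1b | same appointment | the week after |
| 2, questionnaires | BDI-II, HADS by post | same mailing | around the same week, order not fixed |
| 3, interview | MINI, MADRS, HAM-A, covering the last 2 weeks | same visit | the week after |
| 3, questionnaires | BDI-II, HADS | same visit | the week after |

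In no row does coping come from a visit or mailing before the outcome. If 1a and 1b are treated as separate times, as the columns of Table 1 would allow, 1a has no coping measure at all. The only within-time models at 1b then use the BDI-II and HADS, filled in with the Brief-COPE and before EMA coping. The conclusion is the same.

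**Step 3: can the within-phase model tell the directions apart?** This is a simulation under assumptions: standard normal depression score D and coping score C with correlation r, a case being the top 30% of D, a likelihood-ratio test at two-sided 5%, and 1,500 data sets per setting. The article gives neither r nor a significance level for this analysis.
- Depression drives coping: C = r·D + √(1 − r²)·e.
- Coping drives depression: D = r·C + √(1 − r²)·e.

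| N | r | Significant, depression → coping | Significant, coping → depression | Median OR per SD |
|---|---|---|---|---|
| 30 | 0.3 | 26.2% | 24.7% | 1.74 / 1.75 |
| 30 | 0.5 | 59.7% | 58.3% | 2.90 / 2.83 |
| 36 | 0.3 | 29.4% | 28.3% | 1.73 / 1.73 |
| 36 | 0.5 | 67.1% | 66.7% | 2.82 / 2.77 |

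With r = 0, rejection was 5.3% to 6.9%. The simulation error of one percentage near 67% is √(0.67 × 0.33 / 1,500) = 0.012, or 1.2 points, so the two directions cannot be told apart in any row.

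**Step 4: do the planned between-times models solve it?** Assume N = 36, depression acts on coping at phase 1, coping has no effect, and later depression is D3 = 0.6·D1 + 0.8·e. Phase 1 coping and phase 3 depression are then correlated at 0.6·r, that is 0.18 (r = 0.3) or 0.30 (r = 0.5).

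| r | Significant, unadjusted | Significant, adjusted for D1 |
|---|---|---|
| 0.3 | 14% | 6% |
| 0.5 | 29% | 7% |

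Lagging alone leaves part of the reverse effect in the univariate model. Adjustment for the earlier score brings the rate close to 5%. In the simulation D1 is known without error; with a real questionnaire score some of the effect would remain.

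**The case against.** The strongest reply is that the plan already contains analyses with the right time order. The sentence that defines analysis (2) also covers models between times, so coping at 1b against phases 2 and 3, and at 2 against 3, is planned. Analysis (5) fits a multilevel vector autoregressive model to the EMA data, with each variable regressed on the previous time point. It can relate coping at one prompt to symptoms at the next within phase 1. This stands. It rules out the stronger inference that the phase 1 expectation about active coping depends wholly on the within-phase logistic models. That expectation names no analysis and comes directly after the paragraph on time dynamics, so it may well refer to (5). But neither analysis changes what the within-phase models in (2) can show, and the between-times models are univariate.

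A second reply is that predict is ordinary regression vocabulary. That is fair for the word alone, and the text does not establish that effects of depression *will* be reported as coping effects. However, objective 2 also speaks of determinants, so a directional reading is intended at least in part.

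Third, the order is not reversed throughout. Against the BDI-II and HADS, the Brief-COPE is simultaneous. It is also the dispositional version, which might suggest a stable trait. But its instructions were reworded to stroke-related stress and it is first completed after the stroke, so it is not a measure taken before the outcome.

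Fourth, 30 to 36 is the expected EMA sample. The Limitations section keeps patients who decline EMA on the same questionnaires and interviews, so Brief-COPE models could use up to 40 participants (40 × 0.20 = 8 to 40 × 0.40 = 16 depressed cases). This does not affect the question of direction.

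**Conclusion.** The point holds for the within-phase logistic models in analysis (2). At phases 1 and 3 coping is measured with or after every outcome. At phase 2 the Brief-COPE is in the same mailing as the BDI-II and HADS, and the order relative to EMA coping is not fixed. These models can establish association but not direction, so they are not evidence on determinants. That conclusion follows from the schedule alone and needs no assumed effect size.

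The percentages are illustrations under assumed correlations, 30% prevalence and a 5% test. A reader might take the 25% to 67% as false-positive rates of the test. They are not: the simulated association is real, and the figures are the power to detect it. What matters is that they are the same whichever variable is the cause. The lagged figures (14% to 29% unadjusted, 6% to 7% adjusted) also rest on an assumed autocorrelation of 0.6.

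The point concerns one secondary objective. The primary feasibility and validity analyses are unaffected.

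**What to change.** 1. In analysis (2), report within-phase results for coping as cross-sectional associations, and state that they are not evidence for objective 2.
2. Base prediction on coping from an earlier phase against an outcome at a later one: 1b to 2, 1b to 3, and 2 to 3. Replace the univariate model with one that also contains the earlier-phase depression or anxiety score. The BDI-II and HADS are collected with the Brief-COPE at each of these phases, so the score is available.
3. Prefer the continuous later score as the outcome in these models. About 6 to 14 depressed cases will hardly support a logistic model with two terms.
4. In Anticipated Results, tie the phase 1 expectation about active coping to these lagged models or to the autoregressive model in (5).

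The cost is wording and one more term per model; nothing new is collected. Fewer models will be called predictive, and some participants will be lost to drop-out between phases. Adjustment may also remove part of any coping effect that had already changed the earlier score, so the adjusted estimate would be cautious in that respect.
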